#### Mapping frailty to biobank variables

Two models will be used to define frailty and compared. Only one model will be used to consider the overlap with malnutrition and sarcopenia. The 36 deficits model, has been constructed and validated, and applied to large data sets previously [39]. It will be matched to equivalent variables recorded in the UK Biobank. These are listed in S1 Table. The cumulative deficit model calculates the FI by defining the numbers of health deficits present in a person and then dividing by the number of health deficits considered [38, 41]. For instance, a participant with three deficits would have an index score of 3, which out of 36 equals a 0.083 FI. The threshold levels will be: low (robust), where the FI is less than or equal to 0.2; medium (pre-frail), where the FI is more than 0.2 and less than or equal to 0.35; and high (frail), where the FI is more than 0.35. These levels were suggested by Kulminski and colleagues and used in studies that looked at frailty, bone health, and overall mortality [53, 54].

The phenotype model, includes five criteria that will also be mapped with available variables in the UK Biobank. The first four criteria are derived from the self-reported variables entered by participants including: weight loss, exhaustion, slow walking pace and low physical activity. Hand grip strength is a measured variable See Table 2. These criteria were previously used in two studies based on the UK Biobank database [29, 55]. Participants will be classified as robust (met none of the frailty criteria), pre-frail (met one or two of the criteria) or frail (met three or more of the criteria) according to cut-offs described by Fried and colleagues [35]. This is done to ensure consistency with the existing literature, refer to Table 3.

**Table 3 pone.0278371.t003:** Mapping the phenotype model.

Variable	Data Description	Categories Description/Units
weight loss	The information is provided by the participants’ answer to the question ‘compared with one year ago, has your weight changed?’	Response: yes, lost weight = 1, other = 0
exhaustion	Determined by the question ‘over the past two weeks, how often have you felt tired or had little energy?’	Response: more than half the days or nearly every day = 1, other = 0
walking speed	Determined from answers to the question ‘how would you describe your usual walking pace?	(1) slow pace (2) steady/average pace or (3) brisk pace
physical activity	Derived by using both the Total Metabolic Equivalent [MET] and the physical activity questionnaire	
handgrip strength	Cut-points classified according to gender	men less than 30kg women less than 20kg

#### Mapping sarcopenia

The EWGSOP standard definition of Sarcopenia has three criteria that can be mapped to variables in the biobank. Sarcopenia is diagnosed if the person has low muscle mass in addition to criterion two or three. The first is muscle mass measured by bioelectrical impedance and the second is muscle strength, measured by handgrip strength (see Table 2). Finally, physical performance as assessed by the participants’ self-reported answers to the validated International Physical Activity Questionnaire [56].

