## Methods/design of UK Biobank

This is a cross-sectional study using participants recruited to the UK Biobank. The UK Biobank is a population-based prospective longitudinal cohort with information on approximately 500,000 people. Participants were recruited from the NHS aged between 40–69 years. However, the database included participants aged 37 to 73 for the baseline visit. Data were collected for the initial assessment visit between 2007 and 2010. This was termed the baseline assessment that will be used for this study. An invitation was sent by mail to people who were living within a reasonable travelling distance from the assessment centres used for data collection. People were recruited from England, Scotland and Wales.

At the baseline assessment visit, all participants had to be able to give consent before starting the assessment. Then a series of assessment stations where undertaken that included a touchscreen questionnaire and an interview questionnaire about diet, cognitive function, work history and digestive health [49]. In addition to demographic data, the participants were given cognitive function tests, their height, hip and waist measurements were recorded, as well as their bioelectrical impedance measurements and hand-grip strength. The UK Biobank database aims to improve prevention, diagnosis and treatment of a broad number of diseases. This detailed information on participants provides a resource for investigators to conduct research relating to particular diseases [49].

The UK Biobank Ethics and Governance Council (EGC) was founded by the Medical Research Council and Wellcome Trust, allowing them to act independently [50]. The UK Biobank controls all access to and use of the data [50]. However, UK Biobank evaluates all proposals to verify that they would be compliant with the participants’ consent and the Biobank’s Governance Framework and have received the required ethics approval [50]. The researcher and collaborators signed a Material Transfer Agreement (MTA) with the UK Biobank. The MTA was submitted and the payment process completed for the approved application, allowing the data to be released to the approved researcher.

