#### Mapping malnutrition to biobank variables

The GLIM criteria will be applied to variables collected in the UK Biobank database in order to define participants with malnutrition. It includes five criteria, which will be mapped to equivalent variables that are available in the UK Biobank shown in Table 2.

**Table 2 pone.0278371.t002:** Variable mapped to malnutrition, frailty and sarcopenia.

Variable	Data Description	Categories Description/Units of measurement	Malnutrition	Frailty	Sarcopenia
Dietary intake	FFQ and 24-hour dietary recall		X		
Anthropometric measurements	height measured using a Seca 202 height measuring rod and weight measured using Tanita BC-418 MA body composition analyser	Height recorded in centimetre unit Weight recorded in kilograms unit	X	X	X
Body composition	Bioelectrical impedance using Tanita BC-418MA body composition analyser	used to determine body composition fat mass, fat-free mass and body water.	X	X	X
Handgrip strength	Jamar J00105 hydraulic hand dynamometer	Kilogram		X	X

These variables will represent three phenotypic criteria and two etiologic criteria, where patients will be defined as having malnutrition if they have one phenotypic criterion and one aetiological criterion. The three phenotypic criteria are BMI < 22 kg/m^2^ if participants are 70 years or older, or BMI < 20 kg/m^2^ if participants are under 70 years old [21]; weight loss, as reported by the participants’ response to ‘Compared with one year ago, has your weight changed?’; and finally fat free mass index, calculated by dividing fat free mass by height squared (FFMI, kg/m2). The thresholds will be <17 kg/m^2^ for males and < 15 kg/m^2^ for females [20].

The first etiologic criteria, is defined as reduced food intake < 50% reduction of the standard energy requirement for the male group (50–54 years: 2,581 kcal/day, 55–64 years: 2,581 kcal/day, 65–74 years: 2,342 kcal/day) and the female group (50–54 years: 2,103 kcal/day, 55–64 years: 2,079 kcal/day, 65–74 years: 1,912 kcal/day) [51]. The second etiologic criterion is inflammation based on the C-reactive protein (CRP). [11, 52].

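### One impedance measurement feeds both the malnutrition and the sarcopenia definitions, so their overlap will exceed chance partly by construction, and the planned output cannot show by how much

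*Protocol article*

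**What the plan says.** **Malnutrition** (Protocol article, Mapping malnutrition to biobank variables). The rule is: "patients will be defined as having malnutrition if they have one phenotypic criterion and one aetiological criterion". One of the three phenotypic criteria is the "fat free mass index, calculated by dividing fat free mass by height squared (FFMI, kg/m2"). Its cut-offs are fixed: "The thresholds will be <17 kg/m^2^ for males and < 15 kg/m^2^ for females". The other two are low BMI and self-reported weight loss.

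**Sarcopenia** (Mapping sarcopenia). The rule is: "Sarcopenia is diagnosed if the person has low muscle mass in addition to criterion two or three". The measurement is named: "The first is muscle mass measured by bioelectrical impedance". The section gives no muscle-mass index and no cut-off.

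**Source of both** (Table 2). The body composition row names one device, "Bioelectrical impedance using Tanita BC-418MA body composition analyser", and is marked for malnutrition, frailty and sarcopenia. Its outputs are "used to determine body composition fat mass, fat-free mass and body water", so fat-free mass is the only lean-tissue quantity listed.

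**Timing** (Methods/design of UK Biobank). There is one visit: "This was termed the baseline assessment that will be used for this study".

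**Analysis** (Statistical analysis). The article notes that the conditions are not independent and responds with a Venn diagram and a prevalence with confidence interval for each segment. It describes no breakdown by the criterion that placed a person in a segment. Study limitations does not mention a shared measurement, and the Discussion says the sarcopenia criteria were matched without difficulty.

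**The concern.** The stated aim is to explore the overlap of the three conditions. A person with low lean mass on the impedance reading has the compulsory part of sarcopenia and, subject to cut-offs, already has the phenotypic part of malnutrition. Such a person needs only an aetiological criterion to be malnourished and only low strength or low performance to be sarcopenic. The two labels will therefore coincide more often than chance even if nothing else links the conditions.

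Two segments are affected: malnutrition with sarcopenia, and all three conditions together. The problem remains whichever frailty model is chosen for the diagram. With about 381,000 people the segment intervals will be narrow. They describe sampling error only, so a reader could take a precise figure for the co-occurrence of two separate conditions when part of it is one measurement counted twice. The prevalence of each single condition is not affected.

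**Working it through.** **Plan's own figure.** The article states no expected overlap. Its only reproducible design figure is the sample size: 0.76 × 500,000 = 380,000, against 381,000 stated. They agree within rounding, and the point does not depend on it.

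**Set-up.** Let L = low lean mass, B = low BMI, W = weight loss, E = at least one aetiological criterion, F = low strength or low performance.

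- Malnutrition M = E and (L or B or W).
- Sarcopenia S = L and F.

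These rules come from the two mapping sections. The document gives no component prevalences, so all of the following are assumptions: L 2 to 10%, B 3%, W 5 to 25%, E 10 or 30%, F 20%, all components independent.

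**Case 1: same measure, same cut-off.** S then implies the malnutrition phenotype.

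- P(M and S) = P(E) P(L) P(F)
- Ratio to chance = P(M and S) / [P(M) P(S)] = 1 / P(L or B or W)

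The ratio exceeds 1 unless everyone has the phenotype. It needs E and F to be unrelated to the other components and to each other, but L, B and W may be related among themselves.

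Central case (L 5%, B 3%, W 15%, E 30%, F 20%):

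- P(any phenotype) = 1 − 0.95 × 0.97 × 0.85 = 0.2167
- P(M) = 0.30 × 0.2167 = 6.5%
- P(S) = 0.05 × 0.20 = 1.0%
- Overlap = 0.30 × 0.05 × 0.20 = 0.30%; chance = 0.065 × 0.010 = 0.065%
- Ratio = 1 / 0.2167 = 4.6 (simulation with 5 million draws: 4.63)
- In 381,000 people: 1,143 against 248 by chance

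Ends of the assumed range:

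- L 2%, W 5%: 1 / (1 − 0.98 × 0.97 × 0.95) = 1 / 0.0969 = 10.3
- L 10%, W 25%: 1 / (1 − 0.90 × 0.97 × 0.75) = 1 / 0.3453 = 2.9

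**Case 2: same measure, different cut-offs** (B 3%, W 15%, so P(B or W) = 1 − 0.97 × 0.85 = 0.1755). If the sarcopenia cut-off is the looser one, with prevalences Ls > Lg, then P(phenotype given S) = [Lg + (Ls − Lg) × 0.1755] / Ls.

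| Low by sarcopenia cut-off | Low by GLIM cut-off | P(phenotype given S) | P(phenotype) | Ratio |
|---|---|---|---|---|
| 20% | 5% | 0.382 | 0.217 | 1.8 |
| 5% | 2% | 0.505 | 0.192 | 2.6 |
| 10% | 5% | 0.588 | 0.217 | 2.7 |
| 5% | 10% | 1 | 0.258 | 3.9 |

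If the sarcopenia cut-off is the stricter one (last row), S still implies the phenotype and the ratio is again 1 / P(phenotype). With 2% against 5% it stays at 4.6.

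**Case 3: a different muscle measure correlated with FFMI** (both 5% low, bivariate normal). Correlation 0.5 gives 1.7, 0.8 gives 2.7, 0.9 gives 3.2, and 0 gives 1.0.

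**Effect of dropping FFMI.** With all components independent, a BMI and weight-loss phenotype brings the ratio to exactly 1.0. That assumption cannot hold, because BMI = FFMI + fat mass index. I simulated this link, keeping weight loss, E and F independent. Assumptions: equal numbers of women and men; FFMI mean 16.6 and 19.8 (SD 1.3 and 1.7); fat mass index mean 10.5 and 7.5 (SD 4 and 2.8); correlation between the two 0 to 0.5; BMI cut-off 20; weight loss 5 or 15%; common FFMI cut-offs of 15 and 17. The ratio was 4.2 to 7.0 with FFMI in the definition and 1.4 to 3.9 without it.

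**The case against.** **Shared definitions are part of the subject.** The abstract and Background present overlapping definitions as a reason for the study. The analysis is descriptive, and no test of association is planned. A segment validly counts the people who meet both published definitions. This stands, and it means the Venn diagram is not wrong. But a study of overlapping definitions also needs to know how many people overlap through the shared item, and segment totals do not show that.

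**The article does not say that the reading or the cut-off is the same.** This also stands. Mapping sarcopenia speaks of muscle mass and gives no index; that it is the same fat-free mass reading is an inference from Table 2. The Background reports an EWGSOP recommendation of two standard deviations below the mean of healthy young adults, which differs in kind from the fixed FFMI cut-offs. A reader might infer that every sarcopenic participant automatically meets the malnutrition phenotype. That holds only if the sarcopenia cut-off on the same measure is equal or stricter, which the document does not establish. Nor does a sarcopenic person become malnourished without an aetiological criterion.

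**The multipliers are assumed.** Correct. Only the direction comes from the definitions, with the remaining components taken as unrelated.

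**A second Venn diagram could be left to an analysis plan.** In part. The shared component, however, is fixed by the definitions in this article, and its limitations section does not mention it.

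**Conclusion.** The point holds as a structural one. Low lean mass by impedance, apparently from one device at one visit, is sufficient for the malnutrition phenotype and compulsory for sarcopenia. The malnutrition-sarcopenia and triple segments will therefore exceed chance overlap partly by construction, and the planned output cannot separate that part.

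The size cannot be fixed from the document. Under the assumed inputs, the malnutrition-sarcopenia overlap is about 3 to 10 times chance with a common cut-off, and about 2 to 4 times with a different cut-off or a correlated measure. A sarcopenia cut-off stricter than the FFMI one can keep it at the common cut-off value.

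Two stronger conclusions are not supported. The overlap is not shown to be wholly an artefact, since real co-occurrence may be present as well. And a version without FFMI is not free of the shared measurement, since BMI contains fat-free mass. The change is worth making because overlap is the study's aim, but the single-condition prevalences stand as planned.

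**What to change.** Keep full GLIM as the main definition of malnutrition, and then:

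1. In Statistical analysis, tabulate the malnutrition-sarcopenia and triple segments by the phenotypic criterion met (low BMI, weight loss, low FFMI and their combinations), including the number who qualify on FFMI alone.
2. Repeat the Venn diagram with a phenotype of BMI and weight loss only, labelled as a sensitivity analysis, and interpret co-occurrence from both versions together.
3. In Mapping sarcopenia, state the muscle-mass index and cut-off, so that readers can see how far it coincides with the FFMI criterion.
4. In Study limitations, name the shared impedance item.

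The cost is one extra tabulation and one extra diagram on variables already extracted, plus a few sentences. The downside is that the version without FFMI is not full GLIM. It leaves out people who are malnourished on that criterion alone, and it reduces the built-in overlap without removing it.

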The European Working Group on Sarcopenia in Older People (EWGSOP) recommended criteria for diagnosing sarcopenia. These include low muscle mass, low muscle strength and lower physical performance [46]. In order to detect sarcopenia, two parameters are needed pertaining to the amount of muscle and its function. These can be translated into measurable variables: muscle mass, muscle strength, and physical performance [47]. To measure muscle mass, there are many techniques that could be used for assessment. These include computed tomography, magnetic resonance imaging, dual energy X-ray, and bioimpedance analysis [47]. The measurement of muscle strength has fewer validated techniques, and one of the most widely used is handgrip strength because it is easy to use and readily available [48]. Others include knee flexion or extension or peak expiratory flow. There are a number of methods that have been used for physical performance, including the short physical performance battery, gait speed, the timed get-up-and-go test and the stair climb power test [47]. However, the gait speed test is usually used for clinical practice and research [47].

There are different cut-off points when defining sarcopenia that are based on the measurement technique used and the availability of reference standards. The EWGSOP recommends the use of a reference value derived by calculating two standard deviations below the mean from data collected from healthy, young adults rather than other predictive reference population cut-off points [47].

The aim of this study is to explore the overlap between malnutrition, frailty and sarcopenia in an older population, using UK biobank data, by determining the estimated prevalence of these three conditions.

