This proposed research aims to investigate the estimated prevalence of three conditions—malnutrition, frailty and sarcopenia—in people aged 50 years and above who are living in community dwellings using the UK Biobank database. In order to conduct this study, many variables need to be mapped with the available variables in the UK Biobank database. It will be challenging, as not all variables in the diagnostic criteria for malnutrition, frailty and sarcopenia are in the database. For example, the GLIM criteria will be used to identify malnourished older people within the UK Biobank participants. In the phenotypic criteria, we will map weight loss using the participants’ answers to the question ‘compared with one year ago, has your weight changed?’, and not by using the amount of weight recorded. For frailty, the 36 deficits will be matched with the UK Biobank database. However, not all 36 deficits variables were available in the database. For example, the deficit ‘best mobility and transfer problems’ was mapped with an attendance/disability/mobility allowance variable in the database, which has the best-matched information. Although we have made as much effort as possible to match equivalent variables there will be some variables where matches are not as specific as they could be. However, the sarcopenia EWGSOP diagnostic criteria was matched with similar variables in the database with no issue. In addition to these factors the biobank data is not representative of the UK population as a whole [49]. However, the findings of this study will be standardised using data from a second source so the results will be more generalisable.

Other studies have used biobank data and published results mapping definitions of sarcopenia and frailty to available biobank variables [29, 55, 63] and these studies have been considered in this study design.

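### The third sarcopenia criterion, physical performance, is mapped to a physical-activity questionnaire, so people with low muscle mass and normal grip are classified by how active they are

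*Protocol article*

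**What the plan says.** In the protocol article, Mapping sarcopenia gives the decision rule: "Sarcopenia is diagnosed if the person has low muscle mass in addition to criterion two or three". Criterion one is muscle mass by bioelectrical impedance and criterion two is measured handgrip strength. Criterion three is physical performance, taken from "self-reported answers to the validated International Physical Activity Questionnaire".

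The Background summarises the EWGSOP criteria as follows: "These include low muscle mass, low muscle strength and lower physical performance". For performance it names four methods: the short physical performance battery, gait speed, the timed get-up-and-go and stair climb power. It then adds: "However, the gait speed test is usually used for clinical practice and research". No activity questionnaire is among them.

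Table 3, under Mapping frailty to biobank variables, has a walking-speed item taken from self-reported usual pace, with responses "1) slow pace (2) steady/average pace or (3) brisk pace". Physical activity is a different row, derived from metabolic equivalents and a physical activity questionnaire.

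The Discussion admits imperfect matches for weight loss and for the 36 deficits, but says of sarcopenia that "the sarcopenia EWGSOP diagnostic criteria was matched with similar variables in the database with no issue". Study limitations, comparing EWGSOP with its update, describes the dropped criterion as low physical activity.

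**The concern.** Performance is how well a person carries out a physical task. Activity is how much a person habitually does. The protocol keeps the two apart when it defines frailty and merges them when it defines sarcopenia, without giving a reason. The closer stand-in for gait speed, self-reported walking pace, is already being extracted.

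Prevalence and overlap are the study's stated aims. Because criteria two and three are joined by *or*, criterion three alone can turn a person with low mass into a case. A misdirected third criterion therefore feeds into the sarcopenia estimate and into every Venn segment with sarcopenia in it. Age and gender standardisation reweights the strata but does not correct classification within them. With about 381,000 participants, the confidence intervals would be narrow around whatever construct has been measured.

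**Working it through.** **Side by side.** The Background calls the third EWGSOP criterion performance and lists only tests. Mapping sarcopenia keeps the name but measures activity. Table 3 treats walking speed and activity as two criteria, each scoring separately. Study limitations then calls the EWGSOP criterion itself activity. The four places cannot all be right.

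**Who is affected.** From the decision rule:

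- Normal muscle mass: never a case, so unaffected.
- Low mass and weak grip: always a case through criterion two, so unaffected.
- Low mass and normal grip: a case only if criterion three is met, so the choice of variable decides.

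Within the last group, an inactive person with normal walking is counted under the plan and would not be under walking pace. An active person with slow walking is missed under the plan and would be counted under walking pace.

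**Scale.** The article states no sarcopenia prevalence, item prevalence or questionnaire cut-off, so there is no figure to reproduce and every input here is an assumption. Let m be the proportion with low mass and, among those people, g the proportion with weak grip, a with low activity and s with slow pace. Assume the items are independent.

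Prevalence with activity = m × [1 − (1 − g)(1 − a)]. Prevalence with walking pace = m × [1 − (1 − g)(1 − s)]. The ratio of the two does not depend on m. With m = 10%:

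| g | a | s | Activity | Walking pace | Ratio |
|---|---|---|---|---|---|
| 12% | 20% | 8% | 0.10 × (1 − 0.88 × 0.80) = 2.96% | 0.10 × (1 − 0.88 × 0.92) = 1.90% | 1.55 |
| 12% | 15% | 10% | 2.52% | 2.08% | 1.21 |
| 12% | 30% | 5% | 3.84% | 1.64% | 2.34 |
| 30% | 20% | 8% | 4.40% | 3.56% | 1.24 |
| 30% | 15% | 10% | 4.05% | 3.70% | 1.09 |
| 30% | 30% | 5% | 5.10% | 3.35% | 1.52 |
| 50% | 20% | 8% | 6.00% | 5.40% | 1.11 |

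The commoner weak grip is among people with low mass, the less criterion three matters. Every row sets low activity above slow pace, so a ratio above 1 is built in. Swapping the first row (a = 8%, s = 20%) gives 1.90/2.96 = 0.64.

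**Net and gross.** The prevalence difference understates how many people change status. In the first row, among people with low mass, 0.88 × 0.20 × 0.92 = 16.2% are counted only under activity and 0.88 × 0.80 × 0.08 = 5.6% only under walking pace. The net is 10.6% of the low-mass group, which is the 1.06-point gap in prevalence (0.10 × 10.6%). The gross is 21.8%. Equal prevalences under the two versions would not show that the same people were classified.

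**Dependence on criterion three.** The share of cases qualifying through it alone is (1 − g)x / [1 − (1 − g)(1 − x)], where x is the proportion of low-mass people meeting it. For g = 10–30% and x = 5–40% this runs from 10% (g = 30%, x = 5%) to 78% (g = 10%, x = 40%).

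**The case against.** A reader might infer that sarcopenia as a whole is being classified on behaviour, or that none of the resulting estimates reflect EWGSOP. The text does not support that. Low muscle mass is always required, measured grip is an independent route to the diagnosis, and everyone with low mass and weak grip is classified identically under either mapping. Nor does the text support a statement that prevalence will be too high. No questionnaire cut-off is given, and the direction depends on whether low activity or slow pace is the commoner among people with low mass and normal grip.

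Walking pace is not a performance test either. It is a self-reported item with three categories, closer to gait speed but still a proxy. It is also a frailty-phenotype item, as activity is, so exchanging one for the other leaves a shared item if the phenotype model is the one carried into the overlap analysis. Both points stand and limit what the fix can achieve.

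The article does make general disclosures: some variables are self-reported, and some matches are less specific than they could be. It cites a source for the questionnaire and says published mappings of sarcopenia and frailty in this database were considered. A precedent for the choice can therefore be neither confirmed nor excluded. But the general remarks do not tell the reader that activity has replaced performance, and the specific remark on sarcopenia says there was no difficulty. Describing the questionnaire as validated does not say that it was validated as a measure of performance.

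The study is descriptive and tests no hypothesis. That lowers the stakes for inference, but not for a prevalence estimate that depends on the case definition.

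**Conclusion.** The point holds for one limb of the sarcopenia rule. Mapping physical performance to an activity questionnaire contradicts the Background and Table 3, and the Discussion's assurance about the mapping is inaccurate. People with low mass and normal grip are classified on the wrong construct, with errors in both directions.

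The effect on prevalence and on the Venn segments cannot be derived from the documents. Under independence, with low activity 15–30%, slow pace 5–10% and weak grip 12–30% among those with low mass, the ratio of the two prevalences runs from about 1.1 to 2.3. It reverses if slow pace is the commoner, and correlation between the items would change it. The contradiction itself depends on none of these assumptions. Since it concerns the definition of one of the three conditions under study, it should be settled before the estimates are produced.

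**What to change.** 1. In Mapping sarcopenia, define criterion three as a response of slow to the usual-walking-pace item in Table 3.
2. Report the activity-questionnaire version as a sensitivity analysis. Cross-classify the two versions among people with low mass and normal grip, so that changes in both directions can be seen.
3. In the Discussion, replace the statement that the EWGSOP mapping raised no difficulty with one saying that performance is represented by a self-reported proxy.
4. In Study limitations, correct the description of the EWGSOP criterion from low physical activity to low physical performance.
5. State that walking pace also counts towards the frailty phenotype, so some overlap between frailty and sarcopenia is built in by definition.

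A version using muscle mass and grip only would be a useful optional sensitivity analysis. It drops the self-reported item altogether, although grip is also a frailty-phenotype item.

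The cost is small: wording changes, recoding of a variable already planned for extraction, and one additional set of prevalence and overlap estimates. The remaining weakness is that walking pace is still self-reported.
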